### Data Analysis

#### Data Preprocessing

Data preprocessing will be performed with the academic software package Python-MNE [58]. Raw EEG data will be filtered with a zero-phase band-pass filter (0.01-100 Hz). Unpublished results from our preliminary EEG assessments suggest that EEG signals collected in an electromagnetically shielded measurement environment may not need notch filtering for the power line noise removal. The EEG data will be referenced with an average reference. The EEG dataset will be decomposed into independent components using the extended infomax independent component analysis algorithm [59]. The obtained independent components will be visually inspected and compared with EOG and EMG data (using correlation-based analysis). After removing independent components related to artifacts, the EEG data will be reconstructed with the inverse independent component analysis procedure and will be segmented into 1-second epochs.

#### Statistical Analysis

Descriptive statistics will be used to report demographic and baseline characteristics. Quantitative data will be presented as mean, SD, and range (minimum and maximum); qualitative data will be presented as absolute and relative frequencies and, if appropriate, as graphs. We plan to use a linear mixed-effects model to test within-subject and between-group differences in traditional EEG power bands, with the participant group (ie, “tinnitus subject” and “nontinnitus subject”), time-point (ie, “baseline,” “stimulus,” and “poststimulus”), and stimulus type (ie, “RI stimulus” and “control stimulus”) as fixed effects. Subject IDs will be included as a random effect to account for repeated measures. Missing data will not be replaced but treated as “missing” values.

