This study aims to examine the brain activity in tinnitus and nontinnitus subjects using whole-scalp EEG recordings. RI will be used to modulate the tinnitus perception and enable a within-subject comparison. In addition, the RI stimuli will be matched with the tinnitus frequency of each participant, while the same low-frequency (0.5 kHz) control stimuli will be presented to all participants to exclude any effects of nonspecific sound-induced responses. We extend the applicable frequency range up to 13 kHz to enable a more accurate frequency identification of tinnitus and RI characteristics across a wider portion of the audibility range. Moreover, including nontinnitus subjects enables to compare between matched tinnitus and nontinnitus groups (ie, hearing loss characteristics) to determine whether the observed differences in the neuronal activity after RI are tinnitus-specific.

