#### Sample Size

To estimate the appropriate sample size, we used data from a previous study showing statistically significant differences between the PSDs of EEG recordings from tinnitus and nontinnitus participants [53]. The averaged power in the theta band was approximately 15.6 and 14.3 µV^2^ for the tinnitus and nontinnitus subjects, respectively, and the pooled SD was 0.5 µV^2^. A power analysis to test a two-sided hypothesis at a significance level of.05 and a power of 80% was estimated to require a sample size of 39 participants in each group. Up to 50 participants in each group meeting the eligibility criteria after pre-enrollment and the screening session will be recruited.

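### The mixed model as listed has no interaction, so it does not test what the control stimulus and the nontinnitus group are there to show

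*Protocol article*

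**What the plan says.** The Statistical Analysis section says "We plan to use a linear mixed-effects model to test within-subject and between-group differences in traditional EEG power bands". It then gives three fixed effects: participant group (tinnitus, nontinnitus), time-point (baseline, stimulus, poststimulus) and stimulus type (RI, control). Subject is the random effect. No interaction or primary contrast is listed.

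The Background section explains what the design is for. The 0.5 kHz control stimulus is given to all participants "to exclude any effects of nonspecific sound-induced responses". The nontinnitus group is included "to determine whether the observed differences in the neuronal activity after RI are tinnitus-specific".

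The Objectives section places the primary hypothesis in the within-subject change from baseline to poststimulus that is due to RI, in the conventional EEG bands generally. Secondary objectives 2 and 3 ask about the group difference at baseline and the group difference at poststimulus as two separate questions.

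One band, theta, is used in the Sample Size section, for a comparison of tinnitus with nontinnitus participants: "The averaged power in the theta band was approximately 15.6 and 14.3". It is not declared primary.

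**The concern.** The two stated purposes are statements about interactions. Removing the nonspecific response to sound means comparing the change after the RI stimulus with the change after the control stimulus (time-point x stimulus type, in tinnitus subjects). Showing that the result is specific to tinnitus means asking whether that comparison differs between groups (group x time-point x stimulus type). The model as listed contains neither term.

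The interpretation of the main result is at stake. Every poststimulus epoch follows 60 seconds of sound, and the button-press task is described for that epoch only. Some change from baseline that has nothing to do with RI is therefore plausible. If the listed model were fitted literally, such a change could produce a significant time effect, while a real RI effect would be heavily diluted.

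**Working it through.** **Inputs.** The layout is 2 groups x 3 time-points x 2 stimulus types = 12 cells (Statistical Analysis). The article gives no effect size or variance for the within-subject contrast, so the check uses algebra and then an illustration with assumed values.

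**The plan's own figure.** The only planned size is 39 per group, from means 15.6 and 14.3 (difference 1.3); the article adds "the pooled SD was 0.5". The usual formula gives 2 x (1.96 + 0.84)² x (0.5/1.3)² = 2.3, so 3 per group (4 with the t-test). The 39 is not reproduced. That is a separate matter. Here 39 serves only as a group size, because it was derived for a between-group comparison and says nothing about the power of the contrast below.

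**Step 1: what the listed time effect estimates.** In a balanced additive model, poststimulus minus baseline is the average change over the four group-by-stimulus cells.
- A change c common to all four cells: (c + c + c + c)/4 = c.
- A change δ only in tinnitus subjects after the RI stimulus: (δ + 0 + 0 + 0)/4 = 0.25δ.

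**Step 2: what the listed group effect estimates.** The same δ raises one of the six tinnitus cells, so the group coefficient is δ/6 = 0.167δ. The additive model applies this one value at every time-point. The true group differences, averaged over stimuli, are 0 at baseline and δ/2 at poststimulus. Secondary objectives 2 and 3 would receive the same number, and it would be wrong for both.

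**Step 3: what the interaction contrasts estimate.** In tinnitus subjects, (poststimulus - baseline) after RI minus (poststimulus - baseline) after control = (c + δ) - c = δ. The same contrast in controls is c - c = 0, so the three-way contrast is also δ. The common change cancels in both.

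**Step 4: illustration.** Assumptions: 39 per group, one value per subject, time-point and stimulus type, residual SD 1, random subject intercept, 4000 simulated runs, two-sided .05. The table gives rejection rates.

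| Truth | Time effect, listed model | RI minus control, tinnitus subjects | Three-way contrast |
|---|---|---|---|
| No effect | 5.1% | 4.5% | 5.0% |
| Common change of 0.4 SD, no RI effect | 94% | 5.0% | 4.7% |
| 0.4 SD in tinnitus subjects after RI only | 14.6% | 23.2% | 14.0% |

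Hand check of the 94%: the standard error is √(2/(2 x 39 x 2)) = 0.113, and 0.4/0.113 = 3.53, well beyond 1.96. The third row shows that the interaction contrasts are not powerful at this effect size. Their advantage is that they answer the right question.

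**Step 5: variance.** With independent errors of variance σ² per value and subject, a pre-post change after one stimulus has variance 2σ², and one averaged over both stimuli has 2σ²/2 = σ². The difference of two changes has 2σ² + 2σ² = 4σ². That is twice the first and four times the second.

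**Step 6: bands (secondary).** The number of bands and a per-band level are not stated. If 4, 5 or 6 independent bands were each tested at .05, the chance of at least one false positive would be 1 - 0.95⁴ = 18.5%, 1 - 0.95⁵ = 22.6% or 1 - 0.95⁶ = 26.5%. Positive correlation between bands lowers these figures.

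**The case against.** The strongest objection is that silence is being read as a decision. A condensed article often lists the factors of a model without its terms. Nothing in it says the model is additive or that interactions are excluded, and the stated purposes of the control stimulus and control group suggest that interactions or contrasts were intended. A fuller plan may contain them. This stands to the extent that a reader must not infer that the study cannot separate RI from an after-effect of sound: the design can, and only the model as listed does not. It does not dispose of the point. The article does specify factors, levels and the random effect, and that specification does not match the aims stated in the same document.

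A reader might also infer that a difference in any of several bands, each tested at .05, would count as confirmation. The documents do not support this. The .05 level appears only in the sample size calculation, the number of bands is not given, and the hypothesis refers to differences due to RI, which a nonspecific after-effect would not satisfy. The Abstract's feasibility aim also fits exploratory work. Multiplicity rules are commonly left to the full plan.

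Nor does the sample size make theta the natural primary band. Theta sized a between-group comparison, and the group-level RI result cited in the Background is in delta.

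Finally, the interaction contrast does not necessarily remove the button-press task. Participants who experience RI after the control stimulus are excluded, so press timing should differ between RI and control trials. Nontinnitus participants respond to a tone that starts at 37 seconds after either stimulus. This limit stands.

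**Conclusion.** The point holds for the model as listed. In a balanced layout its time effect carries a common after-effect of sound in full and an RI effect confined to tinnitus subjects at one quarter, and it imposes one group difference on baseline and poststimulus alike. It therefore does not test the two purposes given in the Background, and it cannot answer secondary objectives 2 and 3 separately. The one-quarter result needs only balance and additivity; the 94% rests on the assumed 0.4 SD change and the other simulation inputs. The conclusion would lapse if the full plan already contains the interactions.

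The open choice of band is secondary. The 18.5% to 26.5% range is an upper illustration under assumed band numbers, an assumed .05 per band and independence.

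**What to change.** State in the analysis section that the model is group x time-point x stimulus type with all interactions, and name the contrasts:
- Primary: in tinnitus subjects, (poststimulus - baseline) after RI minus (poststimulus - baseline) after control.
- Specificity: the three-way interaction, taken for poststimulus against baseline.
- Secondary objectives 2 and 3: group differences at baseline and at poststimulus as separate contrasts from the same model.

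For the bands, either the sponsor names a primary band before these contrasts are examined, or results are adjusted across bands (for example by Holm) or labelled exploratory. The Abstract reports that data analysis is under way, so naming a band in advance may no longer be possible; in that case one of the other two options applies.

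The cost is analysis wording and precision. No new data are needed. The primary contrast has about twice the variance of a pre-post change after one stimulus and about four times that of one pooled over both stimuli (independent errors). Its power is not covered by the Sample Size section and should be worked out with a stated within-subject variance. Holm lowers the power for individual bands. Possible differences in button-press timing remain and should be acknowledged when the results are interpreted.

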### Objectives

The primary objective of this study is to identify tinnitus-associated neural oscillations in resting-state (spontaneous) scalp EEG data. We hypothesize that differences due to RI in the power spectral density (PSD) of baseline (tinnitus) and poststimulus (reduced tinnitus) measurements within the same subjects can be detected in traditional EEG power bands. The secondary objectives of this project are as follows; (1) to improve understanding of the RI effect on the tinnitus-associated neural activity; (2) to identify differences in the PSD of the baseline period between the tinnitus and control groups; (3) to identify differences in the PSD of the poststimulus period between the tinnitus and control groups; and (4) to evaluate whether within-subject EEG data collection can reduce heterogeneity.

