#### Electroencephalography

EEG recording will be performed with an active electrode 64-channel biopotential measurement system (ActiveTwo, Biosemi). After selection of a suitable EEG head cap and adjustment of the cap position, electrode gel (Signa Gel, Parker Laboratories, Inc) will be injected, and the electrodes will be attached. The position of the electrodes was selected according to the 10/20 standard scheme for 64 electrodes and 2 additional channels for the active common mode sense and passive-driven right leg electrodes. In addition, the three-dimensional coordinates of all electrodes will be recorded. For electrooculography (EOG) and electromyography (EMG) recording, 8 adhesive surface electrodes will be placed at the head of subjects (left and right outer canthus, right infraorbital and supraorbital, left and right masseter, and left and right mastoid). The offset of each electrode will be checked, measured, and, if required, electrode gel will be added until the offset falls within ±40 mV. Participants will be instructed to use a response box for an automated recording procedure (MATLAB script). Trigger events, such as measurement start, stimulus onsets or offsets, and participants’ responses, will directly recorded by the EEG software (ActiView, Biosemi).

EEGs will be recorded during 2 blocks consisting of 12 trials each (Figure 1). Each trial consists of 4 epochs—“Baseline,” “Stimulus,” “Poststimulus,” and “Feedback.” The “Baseline” epoch lasts 40 seconds in which spontaneous resting-state EEG is recorded. During the “Stimulus” epoch, the RI and control stimuli will be presented to subjects through the insert earphones for 60 seconds. The RI and control stimuli are played in a randomized sequence to avoid habituation of neural responses.

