**Figure 1 figure1:**
[figure not shown]
Overview of the electroencephalography recording procedure. RI: residual inhibition.

Subjects are blinded with respect to the order of the stimulation sequence. In the “Poststimulus” epoch, spontaneous resting-state EEG will be recorded for 40 seconds. Tinnitus subjects will be asked to indicate the return of their tinnitus to the normal loudness level by a button press and stay with minimal movement until the end of this epoch. Non-tinnitus controls will be asked to press a button immediately after they perceived a narrow-band stimulus with a central frequency and sensation level same as their matched tinnitus subjects. The stimulus has a duration of 3 seconds and will start 37 seconds after turning off the RI or control stimuli. This process will minimize bias by performing a similar task as tinnitus subjects. In the “Feedback” epoch, EEG recording will be stopped, and participants will be asked to rate the degree of tinnitus loudness change immediately after the stimulus presentation, as well as the change of psychological condition on a scale from −5 to 5 (−5 indicating quieter or feeling less burdened, 0 indicating no change, and +5 indicating louder or feeling more burdened) using the response box. The duration of this epoch is approximately 10 seconds.

Several steps will be taken to suppress or reduce artifacts during EEG recording. The acoustic chamber is electromagnetically shielded. The measurement amplifier is connected by a fiber optic data transfer to the measurement computer outside of the chamber. Before EEG recording is started, light and all power lines will be switched off and no electrical devices, except the battery-powered EEG amplifier, will be active inside the chamber In addition, the chamber will be air-conditioned to avoid contact artifacts of electrodes caused by sweating. During the assessment, participants will be asked to sit relaxed with their eyes closed; they will be instructed to move their body or eyes as little as possible to minimize motion artifacts, especially when making a button press response. To account for muscle and eye artifacts, EOG or EMG are additionally recorded.

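### The planned model leaves a known zero baseline difference unused, so the RI-versus-control contrast is less precise than the recorded data allow

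*Protocol article*

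**What the plan says.** The Statistical Analysis section plans a linear mixed-effects model for EEG band power. Its fixed effects are participant group and "time-point (ie, “baseline,” “stimulus,” and “poststimulus”), and stimulus type (ie, “RI stimulus” and “control stimulus”) as fixed effects". On the random part it says: "Subject IDs will be included as a random effect to account for repeated measures". It names no baseline covariate, no trial-level term and no constraint on the baseline means.

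The Electroencephalography section sets the order of recording: "Each trial consists of 4 epochs—“Baseline,” “Stimulus,” “Poststimulus,” and “Feedback". Baseline therefore always comes before the stimulus of its own trial. The same section states: "EEGs will be recorded during 2 blocks consisting of 12 trials each". On order it says "The RI and control stimuli are played in a randomized sequence to avoid habituation of neural responses", and later "Subjects are blinded with respect to the order of the stimulation sequence".

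The Objectives section states the primary hypothesis as "differences due to RI in the power spectral density (PSD) of baseline (tinnitus) and poststimulus (reduced tinnitus) measurements within the same subjects". Secondary objective 2 compares baseline power between the tinnitus and control groups. The Introduction (Background) gives the 0.5 kHz control stimulus the task of ruling out nonspecific responses to sound.

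**The concern.** A baseline value labelled RI or control carries the label of a stimulus that has not been played, that was placed at random and that the participant cannot foresee. Any observed RI-minus-control difference at baseline is chance. The stated model nevertheless estimates separate baseline levels, or ignores baseline, depending on which terms are fitted and which contrast is read. No reading of it uses the known zero difference.

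The contrast affected is RI versus control. A change from baseline to poststimulus after the RI sound could come from RI or simply from a minute of sound. Only the comparison with the 0.5 kHz stimulus tells them apart, so it carries the attribution to RI in the primary hypothesis. At stake is the precision of that comparison, from data already recorded in every trial.

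**Working it through.** The article gives no figure for the precision of this contrast, so there is none to reproduce. Its sample size calculation concerns a between-group difference and has no bearing here.

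**Inputs**
- From the article: 2 × 12 = 24 trials per participant, with baseline recorded before a randomised stimulus whose order is hidden from the participant.
- Assumed: 12 RI and 12 control trials (the split is not stated), so m = 12; one band-power value per epoch per trial (the unit of a model row is not stated); equal within-participant variance s² at baseline and poststimulus; no carry-over from one trial to the next.
- Not given, so shown as a range: r, the within-participant correlation across trials of baseline and poststimulus power.

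**Variance of the RI-minus-control contrast, per participant**
1. Time-by-stimulus interaction (difference of two mean changes): 2 × 2s²(1−r)/m = 4s²(1−r)/m.
2. Poststimulus difference alone, read from the same model: 2s²/m.
3. Poststimulus difference adjusted for the same trial's baseline: 2s²(1−r²)/m.

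**Ratios**
- (1)/(3) = 4(1−r) / [2(1−r)(1+r)] = 2/(1+r).
- (2)/(3) = 1/(1−r²).

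| r | (1), in s² | (2), in s² | (3), in s² | (1)/(3) | (2)/(3) |
|---|---|---|---|---|---|
| 0 | 0.333 | 0.167 | 0.167 | 2.00 | 1.00 |
| 0.3 | 0.233 | 0.167 | 0.152 | 1.54 | 1.10 |
| 0.5 | 0.167 | 0.167 | 0.125 | 1.33 | 1.33 |
| 0.7 | 0.100 | 0.167 | 0.085 | 1.18 | 1.96 |
| 0.9 | 0.033 | 0.167 | 0.032 | 1.05 | 5.26 |

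The standard error of the interaction is larger by the square root of its ratio: 1.41 times at r = 0, 1.15 at 0.5, 1.03 at 0.9. A simulation with 39 participants and 2,000 runs gave interaction ratios of 1.93, 1.52, 1.31 and 1.18 at r = 0, 0.3, 0.5 and 0.7. For the poststimulus difference it gave 1.00, 1.12, 1.36 and 1.95.

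The two readings cross at r = 0.5. Below that the poststimulus difference is the better of the two, above it the interaction. The better one therefore never costs more than 1.33 in variance, but r would have to be known in advance to choose it. The adjusted contrast is at least as precise as either at every r shown.

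**If participants differ in their RI response.** A between-participant variance t² adds equally to every estimator. At r = 0.5 and m = 12 (t² values assumed):
- t² = 0: 0.125/0.167 = 0.75, a saving of 25%.
- t² = 0.167s²: (0.125 + 0.167)/(0.167 + 0.167) = 0.875, a saving of 12.5%.
- t² = 0.5s²: (0.125 + 0.5)/(0.167 + 0.5) = 0.94, a saving of about 6%.

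**The case against.** The best defence is that baseline has to be an outcome. The primary hypothesis is a baseline-to-poststimulus change, and secondary objective 2 compares baseline power between groups. This stands. A reader might infer that baseline should be a covariate instead of an outcome throughout, with the change only described. The Objectives section does not allow that, so the adjustment belongs beside the existing model, for one contrast.

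A reader might also infer that the RI-versus-control effect is a difference of change scores whatever interactions are fitted. It is not. That holds only for the time-by-stimulus coefficient. The poststimulus difference from the same model subtracts no baseline and loses nothing at r = 0. With main effects only, the stimulus coefficient averages three time-points: an effect of −0.10 confined to poststimulus becomes (0 + 0 − 0.10)/3, about −0.033. That is dilution and a different matter, and the interaction terms may be settled in a fuller plan.

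Two further inferences fail. The labelling does not bias the interaction contrast, because order is randomised. Nor does a covariate remove slow drift in vigilance better than a change score, which already subtracts the same trial's baseline in full.

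It can also be said that this is detail for a fuller plan. That is fair for interactions and covariance. But the article itself makes baseline a level of time-point crossed with stimulus type, and adding interactions or a trial-level term leaves the zero baseline difference unused.

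**Conclusion.** The point holds as one of efficiency for one contrast. As described, the model does not use the fact that RI and control trials have the same expected baseline. The RI-versus-control contrast then has between 1.05 and 2.00 times the necessary variance if read as the interaction, and between 1.00 and 5.26 times if read as the poststimulus difference, for r from 0 to 0.9.

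These factors rest on an r the documents do not give, on an even trial split, one value per epoch per trial, equal variances and no carry-over. They describe trial-level noise only. If participants differ in their RI response, the gain for the group-level contrast is smaller, possibly a few per cent. The validity of the planned analysis is not in question. The change is worth making because it is nearly free and bears on the contrast that attributes an effect to RI.

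**What to change.** Keep baseline as an outcome, as planned, for the primary baseline-to-poststimulus test and for the baseline comparison between groups. For the RI-versus-control contrast, in both groups, specify one of the following in advance:

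- Model poststimulus band power per trial on stimulus type, group and their interaction, with participant random effects. Enter the same trial's baseline power as a covariate, split into the participant's mean and the trial's deviation from it.
- Keep the planned mixed model, but constrain the baseline mean to be equal for RI and control trials within each group, and add a trial-level covariance. Both parts are needed. With participant as the only random effect, baseline and poststimulus of one trial are treated as unrelated beyond the participant's level, so the constraint alone recovers little.

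The control group belongs in this contrast because it shows whether a difference after the RI stimulus is specific to tinnitus.

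The cost is a sentence of analysis wording and one or two degrees of freedom. No further data or participant time is needed.

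### Subject ID as the only random effect does not cover between-subject variation in the baseline-to-poststimulus change, so the primary test can be anticonservative

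*Protocol article*

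**What the plan says.** The primary hypothesis (Objectives) is that differences in power spectral density between baseline and poststimulus "measurements within the same subjects can be detected in traditional EEG power bands". The Statistical Analysis section gives the model: "We plan to use a linear mixed-effects model to test within-subject and between-group differences in traditional EEG power bands". Its fixed effects are group (two levels), time-point (three levels) and stimulus type (two levels). The whole provision for dependence is one sentence: "Subject IDs will be included as a random effect to account for repeated measures".

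The design yields many repeated observations per subject. Under Electroencephalography, "EEGs will be recorded during 2 blocks consisting of 12 trials each". Each trial has a baseline that "epoch lasts 40 seconds in which spontaneous resting-state EEG is recorded" and a poststimulus period in which "spontaneous resting-state EEG will be recorded for 40 seconds". Under Data Preprocessing, the cleaned recording "will be segmented into 1-second epochs". No sentence says whether the rows entering the model are 1-second segments, trials, or averages per subject and condition.

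**The concern.** A subject intercept absorbs differences between subjects in overall power. When poststimulus is compared with baseline in the same subject, it subtracts out. What remains is row-level noise plus the subject's own deviation from the average change. The stated model has no term for that deviation, nor for clustering within a trial. The standard error of the change is then built from a pooled residual that does not fully reflect how much subjects differ in response.

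The article gives good reason to expect such differences. Any loudness reduction of 2 points or more on the −5 to +5 scale qualifies for entry. Tinnitus may be unilateral, bilateral or central. Stimulus frequency and level are set individually. Subjects signal when their tinnitus returns during the poststimulus window, so the inhibited part of that window can vary. The fourth secondary objective is itself about heterogeneity.

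At stake are the p-value and confidence interval of the primary contrast, and whether the result extends beyond the sampled subjects.

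**Working it through.** The plan has no figure of its own for this point. The 39 per group under Sample Size refers to a between-group comparison and does not enter here; the number of subjects cancels below.

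**Inputs from the protocol**
- Trials per subject: 2 × 12 = 24.
- Baseline and poststimulus: 40 s each per trial, cut into 1-second segments, so 24 × 40 = 960 segments per subject and time-point.
- Two-sided 5% level (stated under Sample Size).

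**Assumptions**
- Equal split of stimulus types: 12 trials, or 12 × 40 = 480 segments, per condition.
- τ is the between-subject SD of the true change and σ the SD of one row. The protocol gives neither, so a range of τ/σ is shown.
- Rows are otherwise independent. Positive correlation between neighbouring segments would worsen the 1-second result.

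**Rows below the cell level.** With N subjects and m rows per condition:
- True variance of the mean change: (τ² + 2σ²/m)/N.
- Variance taken by the intercept-only model, if the residual is close to σ²: 2σ²/(mN).
- Ratio: F = 1 + m(τ/σ)²/2.
- Actual type I error: 2 × [1 − Φ(1.96/√F)].

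| Rows per condition | τ/σ | F | Type I error |
|---|---|---|---|
| 480 (1-second) | 0.1 | 1 + 480 × 0.01/2 = 3.4 | 29% |
| 480 | 0.2 | 1 + 480 × 0.04/2 = 10.6 | 55% |
| 12 (trials) | 0.1 | 1 + 12 × 0.01/2 = 1.06 | 6% |
| 12 | 0.3 | 1 + 12 × 0.09/2 = 1.54 | 11% |
| 12 | 0.5 | 1 + 12 × 0.25/2 = 2.5 | 22% |
| any | 0 | 1 | 5% |

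In fact part of τ² leaks into the pooled residual. Allowing for this in a two-condition model lowers the entries slightly: 28.7%, 54.5%, 5.7%, 11.0% and 20.1%. Simulation with 39 subjects gave 28.5%, 53.9% and 20.9% for the first, second and fifth rows.

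**One mean per subject and cell.** Each subject now has 3 × 2 = 6 values. Let v be the variance of the subject-by-time-point deviation and e the remaining variance of a cell mean. The intercept-only residual has 5 degrees of freedom per subject: 2 for subject-by-time-point, with expected mean square 2v + e, and 3 with expected mean square e. The pooled value is [2(2v + e) + 3e]/5 = 0.8v + e. Per subject:
- Change after the residual inhibition stimulus: true variance 2v + 2e, assumed 1.6v + 2e. The ratio rises from 1 towards 1.25, so the error runs from 5% to at most 8%.
- Time-point main effect (baseline versus poststimulus, averaged over stimuli): true 2v + e, assumed 0.8v + e. At v = e the ratio is 3/1.8 = 1.67 (13%). At v = 4e it is 9/4.2 = 2.14 (18%). The limit is 2.5 (about 21%).
- Difference in change between the two stimuli: true 4e, assumed 4(0.8v + e). The ratio is below 1, so this test is conservative.

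**Remedy.** A paired test on one change per subject, which equals a random time-point slope in balanced data, rejected in 4.9% to 5.0% of 20,000 simulated samples of 39 at each τ/σ from 0.1 to 1.0.

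**The case against.** The strongest reply is that the article commits neither to 1-second rows nor to an intercept alone. Segmentation is described under preprocessing and may serve only to estimate the spectrum. Trial, block and segment do not appear as model terms. The listed factors fit six cell means per subject, for which a subject random effect is a familiar formulation. Aggregation level and covariance structure are also often left to a fuller analysis plan, which is not shown.

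Much of this stands. A reader might infer that hundreds of rows per subject will be treated as independent and that the primary p-values will be far too small. The documents do not support that. The rows are unstated. Hundreds fits 1-second segments only, since there are 24 trials per subject. The SD ratios are assumptions, and at trial level with a small ratio the inflation is slight. Nor does the error always run one way: with cell means, the comparison of change between stimuli is conservative.

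Two things remain. The article does more than leave the structure open: it names one term and says that this term accounts for the repeated measures. And the cell-mean reading does not rescue the claim, because an intercept-only model on cell means still departs from 5%, most clearly for the time-point main effect.

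**Conclusion.** Wrong as written. Taken as a random intercept, the stated term does not account for subjects differing in their baseline-to-poststimulus change, so the primary test can be anticonservative. Type I error at a nominal 5% is about 29% to 55% with 1-second rows (ratios 0.1 to 0.2) and about 6% to 22% with trial rows (ratios 0.1 to 0.5). With cell means it is about 5% to 8% for the residual inhibition change and up to about 20% for the time-point main effect. It is 5% if subjects do not differ in their change. These figures rest on the intercept reading, an equal split of stimuli, no serial correlation, and SD ratios that the documents do not supply. That the test can be anticonservative is firm; how badly is not known from the article.

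**What to change.** State the unit of analysis. Then either:
- add by-subject random slopes for time-point, stimulus type and their interaction, plus a trial-within-subject intercept if rows are trials or 1-second segments, with Satterthwaite or Kenward-Roger degrees of freedom; or
- as an alternative, or as the named fallback if that model does not converge, compute each subject's mean change in log band power per stimulus type and test those subject-level changes within and between groups.

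Averaging to cell means and then fitting the intercept-only model is not a substitute. The change takes a sentence or two in the Statistical Analysis section and needs no new data. Its downside is wider confidence intervals for the primary change, which is the price of reflecting real variation between subjects.
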